#### Serious adverse events

6.4.2

Adverse events occur at any dose of the test drug or at any time during the observation period, including death, immediate danger to life, the requirement to be in hospital or prolong hospitalization, disability, and congenital malformation; important medical significance (it refers to those events that will not immediately endanger life or cause death or need hospitalization, but may do harm to patients and need measures to prevent) and medical treatment needed to avoid permanent injury or damage.

#### Severity levels of adverse reactions

6.4.3

Mild: it is usually transient and does not affect daily activities.Moderate: it is quite uncomfortable and affects daily activities.Severe: it makes patients unable to carry out daily activities.

### Observation and records of adverse reactions

6.5

The adverse events record form is set in the CRFs, where researchers are required to fill in the time, severity, duration, measures, and outcomes of adverse events truthfully and to estimate the relationship between adverse events and trials based on 5-level judgment standard.

#### Evaluation criteria for adverse events (including symptoms, signs, and test indexes)

6.5.1

The occurrence time of adverse events coincides with the treatment time;The adverse events are related to the known adverse reactions of the treatment;The adverse events cannot be explained by other reasons;The adverse events will be relieved or disappear after treatment ends;The adverse events will reappear after treating it again.

#### Criteria for adverse reactions

6.5.2

1.*Definitely related*: The occurrence of the reaction conforms to the reasonable time sequence after medication and the known reaction type of the suspected treatment method. The reaction is improved after discontinuation but reappears after treatment again.2.*Probably related*: The occurrence of the reaction conforms to the reasonable time sequence after medication and the known reaction type of the suspected treatment method. The patient's clinical state or other treatment methods may also lead to the same reaction.3.*Probably not related*: The occurrence of the reaction is not quite consistent with the reasonable time sequence after medication and the known reaction type of the suspected treatment method. The patient's clinical state or other treatment methods may also lead to the same reaction.4.*Definitely not related*: The occurrence of the reaction does not meet the reasonable time sequence after medication and some of the reactions cannot be explained by the treatment in the trials. The reaction may take place because of the patient's clinical state or other treatment methods, disappear when the state improves or treatment ends and reappear when using other methods repeatedly.5.*Unknown*: The occurrence of the reaction does not have a definite relation with the time sequence after medication. Both the suspected and other treatments in the trial can lead to the reaction.

The definitely related, the probably related and the unknown can be regarded as adverse reactions of the treatment.

During the trial, researchers are required to observe and fill in the time, severity, duration, measures, and outcomes of any adverse events carefully and to follow up properly. If an abnormal value with clinical significance is found, it should be observed at least once a week until it reaches the normal or baseline level.

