### Treatment methods of adverse events

6.7

All the information on serious adverse events should be collected and recorded in the serious adverse events record form. Necessary measures should be taken immediately to ensure the safety of the subjects when each case of adverse events happens, which should be reported to the ethics committee of the Affiliated Hospital of Liaoning University of Traditional Chinese Medicine.

Common adverse reactions in the process of acupuncture include fainting, bent needles, stuck needles, broken needles, and hematoma. When the patient faint during the acupuncture, stop needling immediately, withdraw all the needles, keep the patient lie flat, and pay attention to keep him warm. In mild conditions, patients can recover after lying on his back for a while without the pillow and drinking warm water or with sugar. In serious conditions, besides the above treatment, patients will get acupuncture at Renzhong (GV26), Suliao (DU25), Neiguan (PC6), and Zusanli (TE3) and get moxibustion at Baihui (GV20), Guanyuan (CV4), and Qihai (CV6). If the patient is still unconscious with weak breath and pulse, emergency measures should be taken into consideration.

When the needle is bent, do not withdraw the needle forcibly in case of breaking the needle and leaving it in the body. If the handle is slightly bent, the needle should be withdrawn slowly; if the angle of bending is too large, the needle should be withdrawn along the bending direction. If the bending is caused by the change of the position, the patient should be slowly back to the original position and the needle should be slowly withdrawn after the local muscles are relaxed.

If the needle is stuck, percuss the needle handle or press the muscles near the acupoints of the needle, or insert another needle nearby. If the sticking of the needle is caused by excessive rotation in 1 direction, twist it back in the opposite direction. Scraping or percussing the needle handle also helps to release the twisted muscle fiber.

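### The five causality classes in section 6.5.2 leave no class for a clear, one-off needle injury and shut a new type of injury out of both related classes

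*Protocol article*

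**What the plan says.** Section 6.5 has the researcher record each adverse event on the CRF and "to estimate the relationship between adverse events and trials based on 5-level judgment standard". Section 6.5.2 defines the five levels:

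- *Definitely related*: "The occurrence of the reaction conforms to the reasonable time sequence after medication and the known reaction type of the suspected treatment method", and in addition "The reaction is improved after discontinuation but reappears after treatment again".
- *Probably related*: the same timing and type condition, and in addition "The patient's clinical state or other treatment methods may also lead to the same reaction".
- *Probably not related*: timing and type do not fit well, and another cause is possible.
- *Definitely not related*: the timing does not fit, and another cause may be responsible.
- *Unknown*: there is no definite time relation, and both the suspected treatment and others could be the cause.

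The section then states which levels count: "The definitely related, the probably related and the unknown can be regarded as adverse reactions of the treatment".

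Two other places bear on this. Section 6.5.1 lists five criteria for judging an adverse event, one of which is "The adverse events cannot be explained by other reasons". Section 6.7 states: "Common adverse reactions in the process of acupuncture include fainting, bent needles, stuck needles, broken needles, and hematoma".

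**The concern.** The levels do not form a complete scale. The first requires a second occurrence. The second is worded around a competing cause. An event that is plainly due to the needle and happens once has neither feature. The ordering is also odd: the same event gains a counted class as soon as another cause becomes possible, so the more doubtful case is easier to count than the clear one.

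Both related classes also require a known reaction type. An injury not seen before with this technique is the kind of event a trial of needles kept around the eyes during training should be able to detect. However good its timing, it cannot be called related on this wording.

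What is at stake is the consistency of the adverse-reaction label and of any count built on it. Six centres will apply the scale, section 5.5 says there is no blinding, and assessors will have to improvise for events the protocol itself foresees.

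**Working it through.** The document gives no figure for this point, so the check is a logical one: apply the wording of 6.5.2 to each possible combination of facts.

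**Step 1. Known type, plausible timing.** Hold timing and type at yes and vary three facts: another cause possible (yes or no), improvement on discontinuation (yes or no), and re-treatment (reappears, does not reappear, not done). That gives 2 × 2 × 3 = 12 combinations.

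| Other cause possible | Improves on discontinuation | On re-treatment | Classes met |
|---|---|---|---|
| Yes | Yes | Reappears | Definitely; probably |
| Yes | Yes | Does not reappear, or not done | Probably (2 combinations) |
| Yes | No | Any of the three | Probably (3 combinations) |
| No | Yes | Reappears | Definitely |
| No | Yes | Does not reappear, or not done | None (2 combinations) |
| No | No | Any of the three | None (3 combinations) |

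With another cause possible, 1 + 2 + 3 = 6 of 6 combinations are counted as adverse reactions. With no other cause, 1 of 6 is counted and 2 + 3 = 5 of 6 meet none of the five classes. The remaining classes do not catch them: both *not related* classes need timing that does not fit, and *unknown* needs an unclear time relation. Over all 12, 6 + 1 = 7 are counted and 5 have no class. These are counts of logical cases, not expected frequencies.

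**Step 2. New type, plausible timing.** Both related classes require the known reaction type, so both fail whatever the other facts are. *Unknown* fails because the time relation is clear, and *definitely not related* fails because the timing fits. *Probably not related* is the only class whose text mentions a poor match with the known type. It also requires timing that is not quite consistent and a possible other cause, so the fit is imperfect. It is nevertheless the class an assessor could be drawn to, and it is not counted.

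**Step 3. Compare the sections.**

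- 6.5.1 against 6.5.2: absence of another explanation is one of the five criteria in 6.5.1. No counted class in 6.5.2 uses it, and *probably related* describes the reverse. Reappearance is one criterion among five in 6.5.1 but a condition of *definitely related* in 6.5.2.
- 6.7 against 6.5.2: 6.7 calls hematoma and broken needles adverse reactions outright. Under 6.5.2 a single case with no other cause and no reappearance cannot be classed as one.

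**The case against.** The strongest reply is that a gap in wording is not a loss of harm data. Much of it stands.

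- **Direction.** A reader might infer that eye-acupuncture harm is under-counted. For known types the text does not show this. The event in the gap does not meet the *not related* classes either. If an assessor picks the nearest class, *probably related* shares its timing and type and is counted. Section 6.7 lists these injuries, which makes filing them as unrelated unlikely, and counting *unknown* pushes the total up.
- **Reach.** A reader might infer that most of the reactions named in 6.7 drop out because they are single mechanical events. That goes too far. Section 4.3 allows body acupuncture in both groups, which is another possible cause, and 6.7 mentions a change of the patient's position as a cause of bending. Section 4.4 gives 5 sessions a week for 4 weeks, 5 × 4 = 20 sessions, so re-exposure is routine and recurrence is possible.
- **Safety analysis.** A reader might take the adverse-reaction rate to be the trial's safety result. The document does not say so. Section 6.4.1 defines adverse events without causality, 6.2 and 6.5 put all of them on the CRF, and 6.6 reports serious events without a causality filter. Which tables are produced is commonly left to the analysis plan, which is not shown.

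The reply does not remove the defect. The five classes are written out in full and are the stated CRF standard, so this is a rule that misfits foreseeable events and not detail left to another document. The point about new types is not answered by the list in 6.7, because a new type is by definition not on it.

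**Conclusion.** The gap is real and can be read directly from the text. With plausible timing, known type and no other cause, 5 of 6 combinations fit no class. With plausible timing and a type not yet known, neither related class is open. The consequence is that such events may be classified inconsistently between unblinded assessors at six centres, and that the adverse-reaction count may be too low, chiefly for new types of injury.

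The size cannot be computed, because the document gives no event rates and does not say how assessors resolve a misfit. The conclusion rests on reading the class definitions literally. A fuller CRF instruction, if one exists, could narrow the gap. The capture of adverse events as such is not affected.

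**What to change.** Reconcile 6.5.2 with 6.5.1 and 6.7, and carry the same wording to the CRF:

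1. Make plausible timing with no other explanation sufficient for a counted related class. Treat reappearance on re-treatment as supporting evidence and not as a requirement.
2. State that an event with plausible timing is not classed as not related only because its type is not yet known.
3. Check that each reaction named in 6.7 has a class when it occurs once and has no other cause.

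With the first change, the five empty combinations in the table fall into a counted class, so 7 + 5 = 12 of 12 are classifiable. The cost is protocol and CRF wording only. The reported adverse-reaction rate may rise slightly.

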### Report on adverse events

6.6

If serious adverse events happen in the trial, the unit undertaking the clinical study should take necessary measures immediately to keep the safety of the subjects and report to the local provincial drug administration and the State Food and Drug Administration (Tel of drug research supervision office of safety supervision department: [name]), the sponsor and the ethics committee in the unit in charge of the study ([contact]), and notify all participating units within 24 hours. The sponsor will ensure to meet all reporting procedures required by laws and regulations.

### Treatment methods of adverse events

6.7

All the information on serious adverse events should be collected and recorded in the serious adverse events record form. Necessary measures should be taken immediately to ensure the safety of the subjects when each case of adverse events happens, which should be reported to the ethics committee of the Affiliated Hospital of Liaoning University of Traditional Chinese Medicine.

Common adverse reactions in the process of acupuncture include fainting, bent needles, stuck needles, broken needles, and hematoma. When the patient faint during the acupuncture, stop needling immediately, withdraw all the needles, keep the patient lie flat, and pay attention to keep him warm. In mild conditions, patients can recover after lying on his back for a while without the pillow and drinking warm water or with sugar. In serious conditions, besides the above treatment, patients will get acupuncture at Renzhong (GV26), Suliao (DU25), Neiguan (PC6), and Zusanli (TE3) and get moxibustion at Baihui (GV20), Guanyuan (CV4), and Qihai (CV6). If the patient is still unconscious with weak breath and pulse, emergency measures should be taken into consideration.

When the needle is bent, do not withdraw the needle forcibly in case of breaking the needle and leaving it in the body. If the handle is slightly bent, the needle should be withdrawn slowly; if the angle of bending is too large, the needle should be withdrawn along the bending direction. If the bending is caused by the change of the position, the patient should be slowly back to the original position and the needle should be slowly withdrawn after the local muscles are relaxed.

If the needle is stuck, percuss the needle handle or press the muscles near the acupoints of the needle, or insert another needle nearby. If the sticking of the needle is caused by excessive rotation in 1 direction, twist it back in the opposite direction. Scraping or percussing the needle handle also helps to release the twisted muscle fiber.

The patient cannot change his original position when the needle is broken. If part of the needle body is exposed outside the body, it can be pulled out with fingers or forceps. If the broken end is flat with the skin or slightly sunk, press the skin around the needle vertically with the thumb and the index finger of the left hand until the broken end is exposed, then remove it with forceps held in the right hand. If the broken needle completely penetrates into the subcutaneous or deep muscle layer, it should be located with an X-ray and removed by surgery.

A small part of subcutaneous hemorrhage or local bruises can heal themselves without treatment. If the local swelling and pain are severe, or the bruises affect the daily activity function, stop bleeding with cold compress first and then do hot compress or gently massage in the local area to promote the local blood stasis dissipation and absorption.

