### Exclusion criteria

3.4

(1)Lacking definitive imaging examination, such as CT or MRI.(2)Special types of stroke: individuals with progressive stroke or intracerebral hemorrhage after cerebral infarction or with disturbance of consciousness.(3)Individuals with mild syndrome; individuals with slight stroke or slight neurological defect and the evaluation of modified Barthel index is more than 70 points; individuals without disability or with rapid improvement of symptoms, such as individuals with the transient ischemic attack (TIA) and (RIND).(4)Individuals who receive treatment of dredging blocking vessels in the acute stage (such as thrombolysis, arterial thrombectomy, super early thrombus aspiration, and stenting).(5)Individuals with bleeding tendency; individuals with serious bleeding within 3 months.(6)Individuals with severe cardiac insufficiency, atrial fibrillation, heart valve disease, or individuals after heart valve replacement.(7)Individuals with other diseases, which can influence the function of limb movement; individuals with limb motor dysfunction caused by claudication, rheumatoid arthritis, or gouty arthritis before treatment.(8)Similar diseases: individuals with CT or MRI imaging of neurological symptoms caused by non-vascular factors; individuals who have suffered from intracranial neurobiology or arteriovenous malformation, aneurysm or neuro-tumor, or individuals with cranial neuro-tumor visible in imaging; individuals with cerebral trauma, multiple sclerosis, cerebral parasites, seizures, hysterical paralysis, or cerebral amyloid angiopathy.(9)Individuals may be exposed to risks or damage by participating in this study from recruitment investigators’ points of view.(10)Disabled individuals (blind, deaf, dumb, mental disorders, mental disorders, and any other limb disability which can affect the evaluation of neurological impairment).(11)Individuals who have known or suspected of having a history of drug or alcohol abuse, or considered inappropriate by the recruitment investigators.(12)Allergic individuals: people who have known or suspected of being allergic to related substances in this study.(13)Individuals who are in other clinical trials or have participated in other drug trials in the past 3 months.

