### Collection and preservation of the baseline data

3.6

We have established the clinical research regulation, standardized operating procedure, data collection, and analysis of the multi-center randomized blind controlled trial. We will collect and evaluate 360 cases of patients with cerebral infarction or intercerebral hemorrhage no more than 3 months and the treatment will last 4 weeks.

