### Normalized operation of eye-acupuncture combined with rehabilitation training therapy

4.1

The rehabilitation programs are determined according to the patient's condition and the evaluation of rehabilitation. Based on the principle for the selection of acupoints, patients receive eye-acupuncture treatment and keep the needles retained in the process of rehabilitation. The rehabilitation training is carried out by physical therapists and the program includes eye-acupuncture physical therapy, eye-acupuncture occupational therapy, eye-acupuncture speech training, eye-acupuncture cognitive rehabilitation training, eye-acupuncture cognitive rehabilitation training, and eye-acupuncture pain rehabilitation techniques. The needles are withdrawn in 5 minutes after the rehabilitation. Researchers should rotate the needle with the thumb and forefinger lightly and slowly until half of the needle is pulled out. Then withdraw the needle slowly and press the hole with a dry cotton ball after pulling out the needle immediately. Pick up the needle and hold the handle with the thumb and food fingers of the needle-holding hand. After gently turning, slowly pull out the needle 1/2, and then slowly pull out the needle (shown in Fig. 2).

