1.*Eye-acupuncture physical therapy*: Eye-acupuncture physical therapy includes eye-acupuncture exercise therapy and eye-acupuncture equipment training. Needles are embedded in the liver region, kidney region, upper-jiao region, and lower-jiao region on both sides. The rehabilitation programs are determined by functional evaluation. Participants are expected to recover or improve dysfunction by taking various kinds of exercise training with hands or equipment, which include limb intelligent feedback training system, gait analysis treadmill, intelligent sports training device, electric erecting bed training, dysphagia therapeutic apparatus, scene interactive rehabilitation system, balance function examination training system, and so on.2.*Eye-acupuncture occupational therapy*: Needles are embedded in the liver region, kidney region, upper-jiao region, and lower-jiao region on both sides of the eyes. At the same time, participants get training and treatment by choosing purposeful activities based on their needs in daily life, family life, social intercourse, and career.3.*Eye-acupuncture speech training*: Needles are embedded in the upper-jiao region, lower-jiao region, heart region, and spleen region on both sides of the eyes for participants with speech disorder. At the same time, conducting the conventional speech training4.*Eye-acupuncture cognitive rehabilitation training*: Needles are embedded in the upper-jiao region, lower-jiao region, heart region, and kidney region on both sides of the eyes. At the same time, rehabilitation treatment for attention, memory, calculation, thinking, the ability to solve problems and execute, and perceptual disorder is implemented in order to improve cognitive function and activity of daily living.5.*Eye-acupuncture pain rehabilitation techniques*: Needles are embedded in the upper-jiao region, lower-jiao region, heart region, and spleen region on both sides of the eyes. At the same time, participants get rehabilitation training based on their major dysfunction.6.*Needles selection*: Specialized needles for eye-acupuncture combined with rehabilitation training therapy at the length of 0.30 mm × 8 mm, 0.25 mm × 8 mm, 0.30 mm × 7 mm, 0.25 mm × 7 mm (Patent Number: CN201320166807).7.*Position selection*: in the supine position.

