### Therapeutic schedule

4.3

Participants are randomly divided into 2 groups and receive different treatments after enrollment.

Basic treatment in 2 groups: taking standardized treatment and the relevant contents in Chinese guidelines for the prevention and treatment of cerebrovascular diseases 2010 and Chinese guidelines for the diagnosis and treatment of cerebral hemorrhage 2014.

The control group: carrying out routine rehabilitation training (for example, physical therapy, occupational therapy, cognitive training, speech training, and swallowing training) on the basis of basic treatment. If participants need body acupuncture treatment, referring to the normalized operation and acupoint selection in body acupuncture above-mentioned.

The experimental group: carrying out eye-acupuncture combined with rehabilitation training (for example, physical therapy, occupational therapy, cognitive training, speech training, and swallowing training). The time of training with needles in the eyes should be less than 6 hours. Needles need to be withdrawn after training. If participants need body acupuncture treatment, referring to the normalized operation and acupoint selection in body acupuncture above-mentioned.

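### The faint procedure in section 6.7 includes a drink of water with no condition on swallowing or alertness, in a trial that admits, treats and tests patients with dysphagia

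*Protocol article*

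**What the plan says.** Section 6.7 (Treatment methods of adverse events) names fainting among the common reactions to acupuncture and sets out its management in steps. Staff are first told to "stop needling immediately, withdraw all the needles, keep the patient lie flat" and to keep the patient warm. For mild cases the text says that "patients can recover after lying on his back for a while without the pillow and drinking warm water or with sugar". The next sentence opens with "In serious conditions, besides the above treatment", so the protocol itself counts the preceding steps as treatment. No sentence in 6.7 makes the drink depend on swallowing or alertness, and sitting up is not mentioned.

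Other sections show who may be in that position:

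- Section 3.4 (Exclusion criteria) does not name dysphagia.
- Section 4.1 lists a "dysphagia therapeutic apparatus" among the training equipment and states that "patients receive eye-acupuncture treatment and keep the needles retained in the process of rehabilitation".
- Section 4.3 describes the experimental arm as "carrying out eye-acupuncture combined with rehabilitation training (for example, physical therapy, occupational therapy, cognitive training, speech training, and swallowing training"). The control arm's rehabilitation gives the same examples.
- Section 5.1.2 lists the water swallow test as a secondary outcome.

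**The concern.** The procedure names fluid by mouth for a patient who has just fainted, in a population where impaired swallowing is expected. Section 3.2.1.1 even lists choking on water among the secondary symptoms of stroke. Water given soon after a faint to someone who swallows poorly, or who is not yet fully alert, can cause choking.

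What is at stake is the safety of individual participants. Sample size, power, error rates and the estimated effect are not affected.

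**Working it through.** There is no figure in the plan to reproduce. The check is a reading of 6.7 against the sections on eligibility, intervention and outcomes, plus simple arithmetic on exposure and on the age of the swallow result.

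**Is the drink part of the procedure?** Yes. It stands under a heading about treating adverse events, and the following sentence refers back to the steps as treatment. The wording is permissive and applies to the mild tier. No claim is made here about the serious tier.

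**Is there a condition on it?** No. The only mention of consciousness in the faint procedure comes later, for a patient who has still not come round, and it leads to emergency measures. Section 6.4.3 defines a mild reaction by its short duration and lack of effect on daily activities, so the word mild does not itself establish alertness or safe swallowing.

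**What posture is described?** Lying flat is the only one named. The text does not say that the drink is taken lying down, but it does not call for sitting up either.

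**Can a participant with dysphagia be in this situation?** Yes, in three steps:

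1. No exclusion in 3.4 names dysphagia. Item 2 excludes disturbed consciousness at entry, which covers neither dysphagia nor a faint during treatment.
2. Swallowing training is among the rehabilitation examples in 4.3, and the needles stay in during rehabilitation under 4.1.
3. A faint with needles in place can therefore happen to someone being treated for impaired swallowing.

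**Scheduled exposure.** Section 4.4 gives one treatment a day, 5 days a week, for 4 weeks. Section 2.3 gives 180 participants in the experimental arm.

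- Sessions per participant: 5 × 4 = 20.
- Sessions in the experimental arm: 20 × 180 = 3,600.

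This is a count of occasions, not of faints. It leaves out body acupuncture, which 4.3 allows in either arm when needed.

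**Age of the latest swallow result.** This bears on the fix only. Inputs are Visit 1 on Day −3 to 0 (5.4.1), Visit 2 on Day 14 (5.4.2) and a window of ±2 days (2.8). Both visits include the secondary outcome scales. Visit days are read as counted from the start of treatment.

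- Before Visit 2: 14 − (−3) = 17 days at most, or 16 − (−3) = 19 days if Visit 2 is two days late.
- After Visit 2, up to Day 28: 28 − 14 = 14 days, or 28 − 12 = 16 days if Visit 2 is two days early.

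A recorded result can thus be more than two weeks old on the day of a faint, so it cannot be the only check.

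**The case against.** The strongest reply is that this is bedside detail missing from a condensed article. The sentence describes how mild cases resolve and does not order staff to give water, and a patient who drinks has presumably come round. Section 3.6 says "We have established the clinical research regulation, standardized operating procedure, data collection, and analysis", and that unseen procedure may hold the precaution. Section 6.7 also carries a general duty to protect participants when an adverse event occurs. Item 9 of the exclusion criteria ("Individuals may be exposed to risks or damage by participating in this study") lets recruiters keep out people at risk, and sites that run the water swallow test know their patients' swallowing status. Finally, the session and day counts do not measure the risk, and the article gives no cut-off for the swallow test on which a fix could rest.

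Several of these points stand. The wording is permissive, the unseen procedure may supply the condition, the number of events may be small, and the counts are not event rates. The missing cut-off means that the fix must also use current clinical status.

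The rest does not remove the problem. The article prints the faint procedure step by step, down to the pillow and the sugar, so the challenge is to a stated step and not to one lost in shortening. The general duty does not qualify the drink. Item 9 works at recruitment and gives no rule for managing a faint. Even a fully alert patient may swallow unsafely, so reading mild as alert answers only half of the concern.

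**Conclusion.** The concern holds. Section 6.7 names a drink in managing a mild faint and attaches no condition to it, although the trial admits, treats and tests patients with impaired swallowing. Followed as printed, the step is unsafe for that part of the population.

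The size of the risk cannot be given, since it would need a faint rate and a dysphagia share and the article has neither. The 3,600 scheduled sessions in the experimental arm show only how often the occasion for a faint arises. Confidence is medium because the wording is permissive and the standard operating procedure is not shown. The change is worth making because the harm is avoidable and the correction costs almost nothing.

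**What to change.** Add one sentence to 6.7: after a faint, fluid by mouth is given only to a patient who is fully alert, is sitting upright and has no known swallowing impairment, judged from the latest recorded water swallow test and from current clinical status; otherwise nothing is given by mouth. Lying flat remains the first step, and the drink is considered only once the patient is alert and able to sit up. If the operating procedure already contains this rule, 6.7 should state it too.

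The cost is that one sentence. It uses a result already collected at Visits 1 and 2 together with bedside judgement, and needs no new test, visit or staff. The only downside is that participants with impaired swallowing go without the drink.

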### Normalized operation and acupoint selection in body acupuncture

4.2

Upper limbs: Jianyu (LI15), Quchi (LI11), Shousanli (LI10), Waiguan (TE5), Hegu (LI4), Yangchi (TE4), Zhongzhu (TE3).

Lower limbs: Huantiao (GB30), Weizhong (BL40), Weiyang (BL39), Yanglingquan (GB34), Zusanli (ST36), Sanyinjiao (SP6), Jiexi (ST41), Kunlun (BL60).

(Taking the recovery stage of stroke in the fifth edition of acupuncture and moxibustion, a textbook for TCM planning in colleges and universities, as reference.)

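### The instruction for serious fainting pairs a point name and a point code that section 4.2 assigns to two different acupoints

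*Protocol article*

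**What the plan says.** Two places in the protocol article bear on this.

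Section 6.7 lists fainting among the common adverse reactions of acupuncture and sets out a graded response. Immediate steps apply to every case, and simple measures are described for mild cases. The serious branch opens with "In serious conditions, besides the above treatment, patients will get acupuncture at" and then names the points: "patients will get acupuncture at Renzhong (GV26), Suliao (DU25), Neiguan (PC6), and Zusanli (TE3"). Moxibustion at three further points follows. If the patient remains unconscious, the text moves on to emergency measures.

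Section 4.2 sets out the body acupuncture points for the trial, each written as a name with a code in brackets. The lower-limb list contains "Yanglingquan (GB34), Zusanli (ST36), Sanyinjiao (SP6"). The upper-limb list ends with "Yangchi (TE4), Zhongzhu (TE3").

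**The concern.** The last needling point in the serious-fainting instruction carries a name and a code that section 4.2 assigns to different points. Someone reading section 6.7 against section 4.2 cannot satisfy both.

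This is an instruction to act during an adverse reaction, not background text, and it applies in a trial run at six centres. Section 4.2 is headed as the normalised operation for body acupuncture, and section 7 treats normalised operation as key to the therapy. A departure from the protocol's own point list in a safety instruction is therefore worth correcting, even though it does not touch the statistical plan. What is at stake is uniform handling of one element of care for serious fainting.

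**Working it through.** No formula applies, because no sample size, error rate or event count depends on this. The check compares name-code pairs.

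**Step 1: the pairs, side by side.**

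| Item | Section 4.2 | Section 6.7 |
|---|---|---|
| Code attached to the name Zusanli | ST36 (lower limbs) | TE3 |
| Name attached to the code TE3 | Zhongzhu (upper limbs) | Zusanli |

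The conflict runs both ways: one name has two codes, and one code has two names.

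**Step 2: is section 4.2 consistent within itself?** It lists 7 upper-limb points and 8 lower-limb points, 7 + 8 = 15 pairs. No name and no code is repeated among them, so section 4.2 gives a unique pairing to compare against. That shows it is coherent. It does not show which section is right.

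**Step 3: does anything else in the article settle it?** No. Zusanli and TE3 appear nowhere else in the text shown, and the article does not say whether the name or the code governs when they disagree.

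**Step 4: how far does the conflict reach?** Section 6.7 names four needling points for serious fainting. The other three (Renzhong, Suliao, Neiguan) and the three moxibustion points (Baihui, Guanyuan, Qihai) do not appear in section 4.2, so they cannot conflict with it. The mismatch is confined to one of the four needling points, in the serious branch only.

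**Step 5: do the two readings differ in practice?** By section 4.2 they do: the name leads to a lower-limb point and the code to an upper-limb point. The difference is one of site, not merely of spelling.

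**Step 6: could it be a reading artefact?** Nothing suggests so. Both places are intact running text in the current article, with no broken table, missing figure, redaction or amendment log involved.

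**The case against.** The strongest case on the other side is that this is a one-label slip close to copy-editing. It touches no endpoint, eligibility rule, randomisation step, analysis set or sample-size input. The article writes these body points with the name first and the code in brackets, and trained operators may work from names and never notice the code. The immediate steps for fainting and the move to emergency measures do not depend on it. All of this stands, and it limits the weight of the point. It does not remove the contradiction, since the article leaves the reader to override one half of a written safety instruction without saying which half.

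A reader might draw four stronger conclusions that the documents do not support.

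- *That staff would needle different points.* Nothing shows that anyone at the six centres works from codes. The text supports only that they could.
- *That case report forms would be ambiguous.* Sections 6.5 and 6.5.2 ask for the time, severity, duration, measures and outcomes of adverse events. They do not say that individual needling points are recorded, by name or by code.
- *That site procedures carry the same error.* Section 3.6 mentions a standardised operating procedure, but it is not shown, and the article condenses a fuller protocol. Whether the slip is repeated there is unknown.
- *That the response to fainting as a whole is unsound.* The contradiction concerns one needling point given in addition to the other steps, which are unaffected.

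It would also be wrong to call this missing detail that an article may leave to a fuller document. Both pairs are stated, and they disagree.

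**Conclusion.** The point holds as a minor internal inconsistency. In the instruction for serious fainting, one of four needling points has a name and a code that section 4.2 assigns to different points on different limbs. Staff following the code could needle a different point from staff following the name.

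The finding rests on the article's text alone and needs no outside knowledge of acupoints. It makes no assumption about which pairing is correct, and this review takes no position on that. That it is a labelling slip is likely but is an inference. There is no effect on design, sample size, power, outcomes or analysis, and nothing in the documents shows that any patient was or would be treated differently. The gain from correcting it is a small one in patient safety and consistency.

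**What to change.** Reconcile section 6.7 with section 4.2 so that the name and the code in the serious-fainting instruction designate a single point, and use the same pairing in both places. The clinical team must decide which point is meant. Check the standardised operating procedure and any adverse-event procedure held at the centres, and correct them only if they contain the same mismatch.

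The cost is one corrected term in the protocol and a short check of site documents. No analysis or sample-size work follows from it. Section 3.5 requires ethics committee approval for any modification of the protocol, so the correction can travel with the next amendment if the clinical team is content with that timing.
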